### Withdrawal from the study

A patient must be withdrawn form the study when judged necessary by the responsible of the protocol or when the patient withdraws his/her informed consent.

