### Data collection

Epidemiological, clinical and all outcome data from each patient will be recorded by the clinician responsible of the study in an electronic database. Psychophysiological data from the Procomp Infinity System will be transformed and recorded in Excel files.

At the end of the treatment, clinicians will arrange a 6 and 12-month review appointment with the patients in the intervention groups and a 12-month review for those in the WL group. At those points clinical follow up data will be collected. A reminder of forthcoming appointments will be distributed to each participant practice 2 weeks before the appointment is due.

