### Trial analysis

Data will be entered in SPSS. Descriptive methods will be used to demonstrate the consistency of the three groups, describe participant characteristics and report levels of participation and drop out. Analysis of variance will be used to evaluate baseline characteristics of the three groups involved in the study, overall significance of improvement across outcome measures, and drop out versus maintainers. For each patient, change in psychometric and physiological measures will be calculated and analysed using t-test for matched groups for both intervention and control groups. The magnitude of change will be estimated and the 95% confidence intervals given.

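### The withdrawal rule takes a patient out of the study, not only out of training, and nothing states that assessment continues, so the between-arm comparison is exposed to bias if withdrawals relate to outcome and differ by arm

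*Protocol article*

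**What the plan says.** Withdrawal from the study consists of one sentence with two triggers. The first is "A patient must be withdrawn form the study when judged necessary by the responsible of the protocol". The second is "or when the patient withdraws his/her informed consent", which is not in dispute here. Since the two are alternatives, the first covers patients who have not withdrawn consent.

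Psychometric assessment schedules the questionnaires for each patient before treatment, on completion, and at 6 and 12 months. Data collection has the review appointments arranged once treatment has ended. Neither section mentions a patient who was withdrawn before then.

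Trial analysis plans the following: "For each patient, change in psychometric and physiological measures will be calculated", with a matched t-test in the intervention and control groups. Analysis of variance is to be used for the overall significance of improvement. On losses, the section will "report levels of participation and drop out" and will compare "drop out versus maintainers".

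**The concern.** The rule as worded merges two events: a patient stops the training, and a patient stops being observed. Only the first can be a decision about the individual's care. The second removes a randomised patient from the data.

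The article relies on randomisation to protect the comparison of VR, non-VR and waiting list. That protection covers the patients as randomised. If patients leave after randomisation on an open judgement, and that judgement is related to how they are doing and operates differently by arm, the remaining groups are no longer comparable. The arm that loses more of its poor responders looks better than it is. Scores that were never collected cannot be recovered at the analysis stage.

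**Working it through.** **Step 1. Follow the text as written.**

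- Withdrawal from the study: on the open judgement, the patient leaves the study.
- Psychometric assessment: after baseline, the next questionnaires come on completion.
- Data collection: review visits are arranged when treatment ends. None is stated for someone who left earlier.
- Trial analysis: change is a later score minus an earlier one. A matched test needs both values, so a patient with only a baseline questionnaire score adds no pair, and has no change score for an analysis of variance either.

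Session-by-session ratings and physiological recordings would exist for the sessions attended. The loss concerns above all the questionnaires at post-treatment and follow-up.

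**Step 2. Could the losses differ by arm?** The document makes this possible but does not show it.

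- The conditions are visibly different (Experimental design).
- Both training arms attend 7 weeks × 2 = 14 sessions (Clinical protocol), while the waiting list has no training. The occasions for a withdrawal judgement are therefore unequal.
- Cybersickness is named as a risk of VR (Potential harms of VR), so one possible reason could arise only in that arm. The article calls it rare.

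**Step 3. Size, under assumptions.** The plan gives no withdrawal figure to reproduce. The only input from it is 25 patients per arm (Subjects). Assumed:

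- no true difference between two arms, with change scores standard normal;
- k patients removed from one arm only, the other arm complete;
- the k removed are those ranked worst on a judgement signal that has correlation r with the change score;
- an unpaired two-sided t-test at 5%; 20,000 simulated trials.

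The large-sample shift in the mean of those who remain is r × φ(c)/(1 − q), with q = k/25 and c = Φ⁻¹(1 − q). At r = 1:

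- k = 3: q = 0.12, shift 0.227 SD
- k = 5: q = 0.20, shift 0.350 SD

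At r = 0.5 these halve to 0.114 and 0.175. The simulation with 25 per arm gives slightly smaller shifts, as expected in a small sample:

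| Removed from one arm of 25 | r = 0 | r = 0.5 | r = 1 |
|---|---|---|---|
| 2 (8%) | 0.00 SD; 4.7% | 0.08 SD; 5.9% | 0.15 SD; 9.1% |
| 3 (12%) | 0.00 SD; 4.9% | 0.11 SD; 7.0% | 0.22 SD; 13.4% |
| 5 (20%) | 0.00 SD; 4.9% | 0.17 SD; 8.9% | 0.34 SD; 24.1% |

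Each cell gives the bias in favour of the depleted arm and the two-sided error rate. The simulation error near 5% is √(0.05 × 0.95 / 20,000) ≈ 0.15 percentage points, so the first column is compatible with no inflation apart from simulation noise.

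**Step 4. Read the table correctly.** The error rates belong to a two-sample comparison, which stands in for one arm against another. They are not the error rates of the within-group matched test that the article names. If the same selection acted in both arms, the expected shifts would cancel in the difference (0.22 − 0.22 = 0), although each arm's own mean change would still be overstated.

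**The case against.** The strongest reply is that the harm comes from silence, and that silence is normal in a condensed article. Criteria for withdrawal, the analysis set and the handling of missing data are commonly settled in a full protocol or analysis plan, neither of which is shown. The article also schedules the questionnaires for each patient and names no completer set. Much of this stands:

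- The absence of an analysis set or a missing-data method is not part of this point.
- That later scores will not be collected is the natural reading of leaving the study, but it is not stated.

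What the reply does not remove is the stated rule itself: mandatory, and worded as leaving the study.

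A reader might infer more than the document supports:

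- *That outcomes are lost selectively and the results are biased.* No number, reason or pattern of withdrawals is given, and poor response is not named as a trigger.
- *That the person who decides on withdrawal also holds the outcomes.* Data collection says that "all outcome data from each patient will be recorded by the clinician responsible of the study", but the article does not say that this is the same person. The sentence concerns entry in a database, and Clinical assessment provides for independent clinicians.
- *That 24% is the error rate to expect.* It is the extreme corner: the five worst responders, one arm only, the other arm complete.
- *That a repeated-measures mixed model would cure the problem.* A patient with only a baseline questionnaire score adds no outcome row when baseline is a covariate, and selection on an unseen outcome is not missing at random. Only continued assessment supplies the information.

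**Conclusion.** The point holds as an exposure to bias, not as demonstrated bias. The withdrawal rule ends study participation where it need only end training, and no other section restores the assessments. Under the assumptions above, with 3 or 5 of 25 patients lost from one arm, the between-arm bias runs from 0 to 0.22 or 0.34 SD and the two-sided error from about 5% to about 13% or 24%. At a moderate correlation of 0.5 it is 0.11 or 0.17 SD, with 7.0% or 8.9%. Where the truth lies depends on the number of withdrawals, their relation to outcome and their balance between arms, none of which the document gives. The change is worth making because it is cheap and later analysis cannot replace it. Confidence is moderate, since a fuller protocol may already provide for continued assessment.

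**What to change.** Leave the decision to stop training exactly as it is. Reword Withdrawal from the study so that the two events are separate, for example:

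> *Stopping training does not end participation in the study. A patient who stops training is still assessed at post-treatment and at the planned follow-up visits, unless consent to data collection is withdrawn, and is analysed in the arm to which he or she was randomised.*

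Then bring three sections into line:

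- **Psychometric assessment:** say that the schedule also applies to patients who have stopped training, and when their post-treatment assessment falls.
- **Data collection:** have review visits arranged for these patients too.
- **Trial analysis:** say that their scores enter the change analyses in the assigned arm, and keep the comparison of drop-outs with maintainers as description, because it shows the loss but does not correct it.

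The cost is a few wording changes and some extra questionnaire contacts, using visits and forms that already exist. No change of statistical model is needed for this point.

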### Clinical assessment

Subjects will be assessed by independent clinicians who will not be involved in the direct clinical care of any of them. They will be psychiatrists, MA-level chartered psychologists or PhD-level chartered psychotherapists. A semistructured interview will be used with the aim of identifying relevant DSM-IV diagnostic criteria for GAD in the subjects.

### Psychometric assessment

The following psychometric questionnaires will be administered to each patient at pre-treatment, upon completion of the clinical trial, and after 6-month and 12-month follow-up periods:

- PSWQ – Penn State Worry Questionnaire – [18]. The PSWQ is the only existing questionnaire specific for GAD with an extensive validation on Italian population. It analyzes symptoms of pathological worries that characterize this disorder.

- BAI – Beck Anxiety Inventory – [19]. The BAI is a standardised and well-used assessment measure with good psychometric properties used to assess anxiety. It is a 21-item scale which covers cognitive, behavioural and physiological symptoms of anxiety.

- Anti – Anxious Thoughts Inventory – [20]. The AnTI included 22 items that investigate 3 different categories of worries: social worries, worries linked to health and the metacognitions about worry (fear of fear). The available data show that the AnTI questionnaire is sensitive to treatment effects.

- CID – Anxiety and Depression Scales of the Clinical Interview for Depression – [21]. The CID anxiety scale consists of 4 items rated on a 7-point scale. The CID depression scale includes 10 items.

- STAI – State-Trait Anxiety Inventory – [22]. The STAI measures a person's situational (or state) anxiety, as well as the amount of anxiety a person generally feels most of the time (trait). The two scales contain 20 items each, which may be scored 1 (not at all) to 4 (very much so).

Immediately before and after each treatment session subjects will be also asked to rate their levels of subjective anxiety on the Visual Anxiety Scale (VAS-A). In order to verify if there is a positive correlation between the treatment efficacy and the sense of presence experienced by the patients during the treatment sessions, the Itc-Sense of Presence Inventory (ITC-SOPI) [23] will be administered to each patient exposed to the VR environment after each session. The ITC-SOPI is a questionnaire composed by 44 items, that investigates the sense of presence experienced during the VR exposure.

Moreover, as homework, patients will be asked to fill some forms regarding their relaxing experiences.

### Psychophysiological assessment

Immediately before and after each treatment session, psychophysiological parameters (skin conductance response (SCR), muscle tension, heart and respiratory rates) will be recorded in order to obtain objective measures of the emotional state of patients. Data will be recorded using the Procomp Infiniti Biofeedback system. The Procomp Infiniti System is an 8 channel, multi-modality encoder used to record different physiological parameters. Connected via USB to the computer, it records 8 parameters in real time and send them to the PC through fiber optic cables. In particular, in this study we are interested in recording 4 parameters: muscle tension, heart rate, respiration and skin conductance, using the following sensors:

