### Experimental design

Patients included in the study will be randomly assigned to one of the following three conditions:

(I) VR: subjects will be taught to relax using VR relaxing environments and audio-visual mobile narratives;

(II) non-VR: patients will be taught to relax using the same relaxing narratives proposed to the VR group, but without the VR support;

(III) WL: patients included in the waiting list group will not receive any kind of relaxation training.

Psychometric and psychophysiological outcomes will serve as quantitative dependent variables, while subjective reports of participants will be used as qualitative dependent variables.

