### Clinical protocol

The clinical protocol will be based on 7 weeks of Applied Relaxation (AR) training (2 sessions per week). Patients will be taught coping skills which enable them to relax rapidly, in order to counteract and possibly eliminate the anxiety reactions.

We will now describe the protocol in details, following the one developed by Ost in 1987 [26]. The sessions will be the same for both groups (VR and non-VR), with the only difference that the VR group is presented with audio narratives accompanied by virtual relaxing environments, while the non-VR group only hear the narratives.

The protocol will follow the following schema:

- Session one: the therapist clearly explains the patient the role of bodily arousal in the maintenance of anxiety and underlines the fact that relaxation procedures can be useful to reduce the autonomic arousal. A general description of the method used in the following sessions will be given to the patient. After an oral presentation, patients will receive a short written description of the rationale. In this way, they will have the possibility to read the text as many times as they want, to ask questions about unclear points and to study it at home.

The following is an example of the text given to the patients (adapted from Ost, 1987):

"When a person suffers from an excessive anxiety usually manifests three different components in his/her reaction: physiological (increased heart rate, blood pressure, sweating etc.), behavioral (trying to escape from the anxious situation, trembling etc.), and subjective (negative thoughts like 'I am going to faint or lose control' etc.). The strength of these components varies between patients, but previous research has found that most people experience some physiological changes, followed by a negative thought, which increases the physiological reaction, generating a vicious circle.

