One good way of breaking this development is to focus on the physiological reactions and learn not to react so strongly. The method we are going to use to achieve this is called applied relaxation. The aim of this technique is to learn a skill of relaxation, which can be applied very rapidly and in any real-life situation. This skill can be compared to any other skill, e.g. learning to swim, ride a bike, or drive a car, in that it takes time and practice to be learned, but once you have mastered it, you can use it anywhere. You are not restricted to the calm and non-stressful situation in the therapist office or your own home.

The goal of the treatment is to be able to relax in few sessions and to use this skill to counteract, and eventually get rid of, the physiological reactions you usually experience in anxious situations. To achieve this we are going through a gradual process starting with tensing and relaxing different muscle groups.

The next step teaches you to connect the self-instruction 'Relax' to the bodily state of relaxation. After that it is time for the rapid relaxation, which you practice many times a day in non-stressful situations. Finally, you reach the stage of applying the skill in anxious situations, and I will take you to different anxiety-arousing situations coaching you how to apply the relaxation at the first signs of anxiety in these situations. Applied relaxation is thus a skill that most people can acquire with the right instructions and practice. It is a 'portable' skill that can be used in almost any situation, e.g. when having problems in falling asleep.

During the entire protocol you'll be guided by relaxing narratives (and images) that suggest you how to reach a relaxed state".

The second part of the session one will be dedicated to fill the following questionnaires: PSWQ, BAI, AnTi, CID and STAI.

The following sessions will be dedicated to teach patients to recognize early signals of nervousness and to cope with anxiety. Each session lasts about one hour and is divided in four parts: homework checking, relaxation, comments about the experience (debriefing) and new homework assignments. Immediately before and after the relaxation phase physiological and psychometric measures will be taken in order to measure the objective and subjective effects of relaxation on the patient. The relaxation setting consists in a very quite room scarcely enlighten in which the patient sits in a comfortable armchair.

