## Discussion

Despite a large number of studies showing the advantages of using VR for the treatment of anxiety disorders (for a recent review see [30]), up to date there is only one study about its potential in stress management and relaxation processes in a sample of non-clinical stressed subjects [15]. What we would like to show with the present study is that VR can facilitate the reduction of anxiety even in a sample of GAD patients. We believe that the use of immersive VR for relaxation represents a promising approach since it enhances the quality of the relaxing experience through the elicitation of the sense of presence. In fact, as reported by different studies [31-34], individuals who interact in environments enriched with a variety of positive visual and auditory stimulations, report greater improvement in self-efficacy and mood. Being able to become relaxed in a certain situation promotes the sense of self-efficacy and prepares participants to cope with real anxiety situations.

Our outcome measures are well-suited to measuring both the subjective and objective impact related to the intervention and the presence of a non-VR group and of a WL list group will guarantee that the results eventually found are really attributable to the intervention. This controlled trial will be able to evaluate the effects of the use of VR in relaxation while preserving the benefits of randomization to reduce bias. Its design takes into account the need for internal and external validity and that the results are attributable to the intervention. Since the international scientific community is now starting to widely recognize the potential of VR as clinical tool [35] we look forward to adding the results of this trial to the growing body of literature in this area.

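### Physiology and VAS-A are scheduled only around treatment sessions, which the waiting-list arm does not have, so their planned analysis cannot include that arm

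*Protocol article*

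**What the plan says.** Timing of the measures:

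- Psychophysiological assessment: "Immediately before and after each treatment session, psychophysiological parameters (skin conductance response (SCR), muscle tension, heart and respiratory rates) will be recorded".
- Psychometric assessment gives VAS-A the same timing, before and after each treatment session.
- Clinical protocol places the readings slightly differently, but still inside a session: "Immediately before and after the relaxation phase physiological and psychometric measures will be taken".

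Who has sessions:

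- Clinical protocol describes them for the VR and non-VR groups only.
- Experimental design says of the third arm: "patients included in the waiting list group will not receive any kind of relaxation training".

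Use of the data:

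- Experimental design makes psychometric and psychophysiological outcomes the quantitative dependent variables of the three-condition trial.
- Trial analysis plans that "change in psychometric and physiological measures will be calculated and analysed using t-test for matched groups for both intervention and control groups". It also plans an analysis of variance of improvement across the outcome measures.
- Discussion states: "Our outcome measures are well-suited to measuring both the subjective and objective impact related to the intervention". It adds that having both a non-VR and a WL group secures attribution of the results to the intervention.

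**The concern.** The measurement schedule and the analysis section do not fit together. The analysis treats physiological change as available in intervention and control groups alike, but the schedule produces such data only where there is a session.

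Two things are at stake. First, a planned analysis has no input for one of the three randomised arms. Second, what remains is a set of before/after tests within each trained arm. The readings bracket a period in which the patient sits in a comfortable armchair in a quiet, dimly lit room. A fall in arousal over that period may come from the training, from the rest, or from both, and a within-arm test cannot tell them apart. A reader of the Discussion would take it that the objective outcomes have an untreated comparator. As scheduled they do not.

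**Working it through.** The protocol gives no figure to reproduce here. The check sets the schedule against the arms and the analysis.

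**Step 1. Count the session-bound measures.** Muscle tension, heart rate, respiration and skin conductance (Psychophysiological assessment) are four signals. VAS-A (Psychometric assessment) is the fifth: 4 + 1 = 5.

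**Step 2. Establish what reaches each arm.**

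| Assessment | VR (25) | non-VR (25) | WL (25) |
|---|---|---|---|
| PSWQ, BAI, AnTI, CID, STAI at fixed times | yes | yes | yes |
| Four physiological signals, before/after | yes | yes | none stated |
| VAS-A, before/after | yes | yes | none stated |

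The questionnaires are given to every patient at fixed times. Data collection adds a 12-month review for WL that gathers clinical follow-up data, with no mention of physiology or VAS-A.

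**Step 3. Count the patients with data.** For the five session-bound measures, 25 + 25 = 50 patients have scheduled readings, and 75 − 50 = 25 (the whole WL arm) have none. A matched t-test in WL has no pairs. An analysis of variance on these measures has two arms, not three.

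**Step 4. Decide what control means in Trial analysis.** The term is not defined there. Data collection contrasts the intervention groups, in the plural, with the WL group. Hardware calls the two trained arms the experimental groups. On that usage control most naturally means WL.

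**Step 5. See what the within-arm tests can show.** Each compares a reading after relaxation with one before it in the same patients. Training and rest occur together in every pair, so the mean change estimates their sum. The two trained arms have the same sessions and differ only in the VR component, so the VR minus non-VR difference removes whatever the setting contributes equally to both. That contrast can be estimated from the data as scheduled.

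**Step 6. Note the repetition.** Training runs 7 weeks × 2 = 14 sessions. Sessions 2–5, 6–9 and 10–13 carry the relaxation and exposure work: 4 + 4 + 4 = 12. Each trained patient therefore contributes about 12 before/after pairs per measure, or up to 14 if every session is counted. A single matched t-test does not account for these repeated pairs.

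**The case against.** The strongest reply is that control is undefined and could mean non-VR. Hypothesis I compares VR with a traditional relaxation protocol, so non-VR is a control in the trial's own main question, and it does have physiology. On that reading the t-tests can be run. This is fair as far as it goes, but the wording of Data collection and Hardware favours WL. Even if non-VR is meant, the three-condition role given to physiology in Experimental design still fails for WL, and within-arm tests still cannot separate training from rest.

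A second reply is that this is silence in a condensed article. It is true that a fuller document might schedule WL recordings. But the article is not silent on timing: it states when these measures are taken, and every stated time lies in or around a session.

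A third reply is that the harm is limited, and this stands. The VR versus non-VR contrast on physiology is intact, neither hypothesis needs a physiological comparison with WL, and the Discussion rests attribution on both comparison groups, not on WL alone.

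A reader might also infer three stronger things that the document does not support:

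- *That power falls below the stated 0.90 because WL physiology is absent.* The 0.90 belongs to a three-group difference at f ≥ 0.40 and is not tied to physiology. VR versus non-VR is 25 against 25 for every outcome, questionnaires included.
- *That patients rest for most of an hour between readings.* The one-hour session has four parts, and Clinical protocol places the readings around the relaxation part only. Sessions 10–13 add exposure to feared situations, so they are not simply quiet sitting.
- *That the matched tests would come out significant from rest alone.* No figure in the document allows that prediction. The point is that the tests could not distinguish the two explanations.

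**Conclusion.** The point holds. As scheduled, five measures have readings in two arms (50 patients) and none stated in the third (25 patients). The three-arm use of physiology and the matched t-tests of physiological change therefore cannot include WL. Within-arm change in the trained arms is not evidence of a training effect, because it is confounded with the setting.

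The conclusion assumes that the stated recording times are complete and that WL patients attend no sessions. Reading control as WL strengthens it but is not essential. Its reach is limited to the four signals and VAS-A. This gap does not touch WL comparisons on PSWQ, BAI, AnTI, CID and STAI, or VR versus non-VR on physiology. It should be corrected because it changes what the trial can claim from its objective measures, but it does not undermine the questionnaire comparison.

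**What to change.** In Trial analysis, state that physiology and VAS-A are compared between VR and non-VR only. Replace the within-arm matched t-tests, as evidence of effect, with a VR minus non-VR contrast of the post value adjusted for the pre value. Account for the repeated sessions per patient, for example with a mixed model that has a patient effect. Within-arm changes can still be reported descriptively. Limit three-arm analyses, and the Discussion's attribution claim against WL, to the five questionnaires.

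This costs only changes of wording and analysis. The downside is that no claim on objective measures against no treatment can then be made.

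If that claim is wanted, the alternative is to record physiology and VAS-A in all three arms at common time points, such as pre-treatment and end of treatment. That costs extra recording visits or procedures, including for the 25 WL patients.
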